**DNA extraction, library preparation and shotgun metagenomic sequencing**

Metagenomic DNA from stool samples will be extracted using MagPure Stool DNA KF Kit B (MAGEN, Guangzhou, China) according to manufacturere instructions. Library preparation is perfored using MGIEasy Universal DNA Library Prep Set (MGI-Shenzhen, China). Genomic DNA will be subjected to fragmentation processing. Fragmented samples are size selected through magnetic beads and converted to blunt-end DNA with end repair reaction. A single Adenosine nucleotide is added on the 3’ end of DNA through the A tailing reaction library adapters are connected to the two ends of DNA by adaptor ligation. Finally, the library products are amplified through PCR reaction and subjected to quality control process. The final double strand library products are denatured to generate the single stranded library product. Then, the circularization reaction is set up to get single stranded circularized DNA products. Any single strand linear DNA will be digested to remove. The final single strand circularized library is amplified with phi29 and rolling circle amplification (RCA) to generate the DNA nano ball (DNB) which carries about 300 copies of the initial single stranded library molecule. The DNBs are loaded into the patterned nanoarray and sequencing reads of PE150 bases length are generated with DNBSEQ-G400 platform (BGI-Shenzhen, China).

**Monitoring and evaluation strategy**

The monitoring and evaluation of the entire project will be conducted at all levels. Data entry will be randomly rechecked for accuracy by re-interviews or re-visits to households participating in the study. The principal investigator oversees the data collectors and enumerators. Bimonthly assessments will be performed by the project team consisting of the project manager, the PI, and the co-PI. In addition, the KMU ORIC team will monitor the overall progress of the project through its own monitoring and evaluation system. Any discrepancy or deviance from the main objectives or lapse in the timeframe and data collection procedures will be handled in close coordination of the project team with the field data collector and support from KMU.

### Participants retention strategies

A common issue in longitudinal cohort studies is systemic attrition, which can have a significant impact on the generalizability of the outcome of interest. Study participants may lose interest in the study and therefore decline their participation, especially in long-term cohort studies. Below is a list of the potential reasons for attrition in the current project and mitigation strategies.
1.The first and most important reason might be that some participants left the study district permanently and left the research team unable to track and collect data at different time points. To tackle this issue, we have set our inclusion criteria such that only those participants who are permanent residents of these districts and who confirm that they have no plans to move outside the district permanently will be recruited.2.Reducing barriers to participation by hiring local research assistants and their training, ensuring anonymity, translating the data collection tools to the local language (Pashto), and pilot testing.3.A follow-up and reminder strategy was set up by calling the participants before data collection.4.Tracing via alternative phone numbers and visiting the house physically when participants did not respond.

### Data analysis

The raw sequencing data will be processed using metapi pipeline (
https://github.com/ohmeta/metapi) followed by quality control process using standards for filtering and trimming the reads (average Phred quality score ≥ 20 and length ≥ 30) using fastp v0.20.1 . Human reads will be removed using Bowtie2 2.4.2 (human genome GRCh38). Taxonomic profiling of the samples will be performed using Kraken2 with standard bacterial, viral, and eukaryotic databases. Diversity assesment will be performed using the MicrobiotaProcess package. Differences in the alpha diversity will be estimated using the Wilcoxon rank sum test. Bidimensional visualization (Beta diversity) will be measurted using non-metric multidimensional scaling and the Bray–Curtis dissimilarity metric implemented in MicrobiotaProcess packages for GNU/R. The ADONIS function was used for obtaining differences in the taxonomic compositions between the groups. Assessment of the differentially abundant species will be done using the metagenomeSeq package.
^
30
^ An adjusted p-value ≤ 0.05 will be considered statistically significant.

We will seek to identify any correlations between the collected metadata and microbiome composition, and identify any gutmicrobiota trends associated infant demographic characteristics, dietary intake (IYCF data), nutritional status (weight for height, weight for age, and height for age and BMI for age z-score, MUAC and head cicrumference) health record (history of diarrhea, upper respiratory tract infections, antibiotic use and duration etc). We will also decorticate the changes in infant gut microbiome in relation to mother dietary intake data (collected though DQQ) and nutritional status (BMI). All postprocessing and statistical analyses will be performed in R.

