## Abstract

Recent evidence suggests that the development of gut microbiota during infancy affects several metabolic, immune, and endocrine pathways in humans. An imbalance in gut microbiota diversity or function, also known as dysbiosis, not only affects early child growth and development, but is also linked with the development of chronic, non-communicable diseases in later life. The
**C**hild
**H**ealth
**A**nd
**M**icrobiome Development Study –
**P**akistan (CHAMP) study aimed to longitudinally assess gut microbiota development and associated factors (maternal, child, and demographic) during early childhood in populations residing in malnutrition-endemic communities in Pakistan. A prospective cohort of mother-infant pairs (n=70) will be recruited from District Swat, Pakistan, and followed for two years. Complete information about demographic characteristics, anti-natal and post-natal care, dietary intake, feeding practices, and child health will be collected at baseline and 3, 6, 12, 18, and 24 months. Anthropometric measurements (height, weight, mid-upper arm circumference, and head circumference), dry blood spots, and fecal samples were also collected. Ethical approval for the study was obtained from Khyber Medical University, Pakistan. The study is also registered on
clincaltrial.gov (Ref no: NCT05793294). The study findings will help researchers understand gut microbiota development, associated factors, and their impact on longitudinal growth in infants during the first two years of life.

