## Introduction

Infancy, the period from birth to around two years of age, is a crucial stage in human development, characterized primarily by rapid physical, mental, and emotional growth.
^
1
^ During this period, many environmental factors such as gestational age, sex, ethnicity, dietary intake, nutritional status, and socioeconomic conditions significantly affect child growth, development, and overall health.
^
2,
3
^ However, to date, these factors, either alone or synergistically, have failed to explain the overall spectrum and variations in children. Recent studies have emphasized that apart from the intersection of environmental factors, the gut microbiome also plays an important role in mediating growth and development, especially during infancy.

The human fetus is believed to develop in a microbe-free environment.
^
4
^ However, immediately after birth, the infant gut, especially the distal ileum and colon, is rapidly colonized by different microorganisms (bacteria, fungi, archaea, and viruses) via vertical transmission from maternal body sites such as the vagina, skin, oral cavity, and gut.
^
5
^ In newborn infants, the gut microbiota exhibits low diversity, consisting mainly of facultative anaerobic bacteria, such as
*Proteobacteria* (e.g.,
*Escherichia* and
*Enterobacter*) and
*Firmicutes* (
*Staphylococcus*,
*Enterococcus*and, and
*Streptococcus*).
^
6
^ Early colonization has a profound influence on the gut environment and subsequent colonization by obligate anaerobes, such as
*Bifidobacterium, Bacteroides* and
*Clostridium.* The relative abundance of
*Bifidobacteria* gradually increases 3 – 4 days after birth and becomes a predominant bacterial genus when the baby is approximately 1 month old.
^
7,
8
^ In healthy growing children, the gut microbiota gradually increases in complexity with a highly diverse microbial composition during and after the first two–three years of life.
^
9
^ During this period, the patterned ecological assembly of microbes occurs mainly under the influence of delivery mode, type of feeding, complimentary feeding practices, antibiotic use, and geography.
^
9–
12
^ Gut microbiota development during early life affects several metabolic, immune, and endocrine pathways and is thus intimately linked to child growth and development.
^
13

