### Sampling technique

District swats are divided into seven administrative units known as Tehsil Municipal Administration units (TMAs). Of these, tehsil Matta was chosen as the study area because it is the second most populated tehsil in Swat district, located at a high altitude with the longest adjoining borders with Dir district (Upper), which has the highest number of rural and remote communities. The Matta tehsil is further divided into union councils, which are the primary administrative institutions in Pakistan. In rural areas, union councils are referred to as village councils. Of the 13 village councils in the sampling area, three union councils will be randomly selected as the primary sampling unit. Subsequently, the researchers visited the primary health centers and designated vaccination centers within the chosen village councils. Newborn children will be identified using the Extended Program for Immunization (EPI) register. Potential participants will be appraoched with the help of Lady Health Workers (LHWs), community-based health workers linked to local health facilities. All families in the area are registered with a designated LHW who regularly visited them. Important information, such as the child’s name, father’s name, date of birth, and address, will be recorded, and a list of eligible study participants will be prepared. Once recruited, each participant will be followed up for two years. The study follows ethical principles involving human subjects as outlined in the declaration of Helsinki. Ethical approval for this study was granted by the Ethics Board of Khyber Medical University, Pakistan ref no DIR/KMU-EB/BR/001-03 dated 11/01/2024.

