### Participants selection

The study population will include 70 mother-infant pairs (dyads), according to the following criteria:

Inclusion criteria
•Apparently healthy infants of both genders aged 0 – 28 days•Born by natural or caesarean delivery•Born to parents from district Swat•Parents/caregivers have no plans to move out of the stud site for at least two years after enrollment in the study.

The exclusion criteria are:
•Child born to an underage (<18 years old) mother.•Infants born with severe acute or chronic medical conditions that require hospitalization, prolonged use of medication, or both, or diagnosed with enteropathies.•Weight of the child is <1500 gm.

Ethical approval for the study was granted by the Research Ethics Board of Khyber Medical University. This study was also registered at
www.clinicaltrial.gov (NCT05793294).

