### Study status

The study began in 2024 and will continue until May 2026. As of October 2024, 70/70 (100%) were recruited. Data and samples were collected for the baseline (n=70) and first follow-up periods (3 months; n = 66).

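### Age at stool sampling is not in the stated exposure comparisons, so it can confound associations with age-linked exposures, chiefly at baseline (0–28 days) or if visits are pooled

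*Protocol article*

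**What the plan says.** The protocol article's Data analysis section names four tools: the Wilcoxon rank sum test for alpha diversity, ADONIS for composition between groups, metagenomeSeq for differentially abundant species, and a general search for associations: "We will seek to identify any correlations between the collected metadata and microbiome composition". The metadata include feeding practices, illness, antibiotic use, anthropometric z-scores, MUAC and head circumference. No tool is given age, visit or any other covariate. The decision rule is "An adjusted p-value ≤ 0.05 will be considered statistically significant", where the adjustment applies to the p-value and not to covariates.

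Participants selection sets the age at entry: "Apparently healthy infants of both genders aged 0 – 28 days". Data "will be collected at baseline and 3, 6, 12, 18, and 24 months" (Abstract). On what happens inside the baseline window, the Introduction describes how the share of Bifidobacteria changes: "gradually increases 3 – 4 days after birth and becomes a predominant bacterial genus when the baby is approximately 1 month old". The Introduction and Discussion also describe rapid change in composition and diversity over the first two years.

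Sampling technique says that date of birth is recorded, and Data collection lists age as a questionnaire item. The secondary objective concerns composition at different time points.

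**The concern.** By the article's own account, age drives the outcome. Several exposures under study also change as infants grow: complementary feeding, accumulated illness and antibiotic courses, and raw MUAC and head circumference, which the text does not clearly standardise for age. Where an exposure and the microbiota both follow age, a comparison without age attributes to the exposure some of what belongs to age. The motivating hypothesis is that malnourished children carry an immature microbiome. Immaturity only has meaning relative to age, so a comparison that does not hold age fixed cannot separate an immature community from a younger child.

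The secondary objective rests on these associations. Adjusting p-values for multiplicity does not remove a bias of this kind.

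**Working it through.** The article gives no error rate, power or effect size, so there is no figure of its own to reproduce. The check asks how far a rank sum test departs from its nominal 5% when the exposure has no effect at a given age.

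**Inputs from the article.** 70 infants; baseline age 0–28 days; six visits (baseline, 3, 6, 12, 18, 24 months), so at most 70 × 6 = 420 samples; rank sum test for alpha diversity.

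**Assumptions (not in the article).** Binary exposure with about half exposed; correlation rx between the exposure's latent scale and age; correlation ry between alpha diversity and age; age uniform over 0–28 days at baseline; a single test at 0.05.

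**1. Hand approximation.** With no true effect, the exposure–diversity correlation created by age is rx × ry. Splitting the exposure at its median multiplies this by √(2/π) = 0.798. The shift in the test statistic is δ ≈ 0.798 × rx × ry × √n, and the rejection rate is Φ(δ − 1.96) + Φ(−δ − 1.96). At baseline, n = 70:

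- rx = ry = 0.2: δ = 0.798 × 0.04 × 8.37 = 0.27, rate 0.06
- rx = ry = 0.4: δ = 0.798 × 0.16 × 8.37 = 1.07, rate 0.19
- rx = ry = 0.6: δ = 0.798 × 0.36 × 8.37 = 2.40, rate 0.67

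**2. Simulation, baseline only** (2000 runs; Monte Carlo standard error at 5% is √(0.05 × 0.95 / 2000) = 0.005). The comparator is a linear model with the exposure and exact age.

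| rx | ry | Rank sum, no age | Linear model with age |
|---|---|---|---|
| 0 | 0.2 / 0.4 / 0.6 | 0.040 / 0.048 / 0.050 | 0.045 / 0.050 / 0.053 |
| 0.2 | 0.2 / 0.4 / 0.6 | 0.051 / 0.075 / 0.137 | 0.045 / 0.046 / 0.057 |
| 0.4 | 0.2 / 0.4 / 0.6 | 0.072 / 0.188 / 0.366 | 0.049 / 0.054 / 0.050 |
| 0.6 | 0.2 / 0.4 / 0.6 | 0.124 / 0.380 / 0.745 | 0.047 / 0.049 / 0.051 |

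The simulation agrees with the hand approximation at 0.2 and 0.4 and is somewhat higher at 0.6. The age-adjusted model stays nominal throughout, although here it has the advantage that the simulated age effect is linear.

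**3. Simulation, by visit against pooled** (500 runs; standard error at 5% about 0.010). Repeated samples were drawn as independent so that only age acts.

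- 12-month visit alone, all infants at one age: 0.04 to 0.07 in every scenario, which is nominal.
- All 420 samples in one test without age: 0.10, 0.76 and 1.00 at rx = ry = 0.2, 0.4 and 0.6; 0.03 to 0.06 when rx = 0.

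The problem therefore depends on two things: whether the exposure follows age, and whether the compared samples differ in age. A later visit kept close to its nominal age is largely safe. Baseline is not, and neither is a pooled analysis.

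**The case against.** The strongest objection is that a condensed article may leave covariates to a fuller plan. ADONIS and metagenomeSeq both accept covariates, so their silence is not a decision to omit age. That stands, and it limits the point for those two tools to a request to state the term. It does not cover alpha diversity: the rank sum test is a stated choice, and no later covariate list can be attached to it.

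Second, the secondary objective's reference to different time points suggests by-visit comparison, which removes most age variation at later visits. This also stands as a likely reading, but the Data analysis section does not confirm it, and by-visit analysis leaves the 28-day spread at baseline. If visits are timed from enrolment and not from birth, which the article does not settle, the same spread carries into the 3-month visit.

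Third, a reader might infer more than the article supports:

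- That age confounds every time-varying exposure. It does not: weight-for-age, height-for-age and BMI-for-age are age-standardised, and an exposure unrelated to age among the compared samples is not confounded by it.
- That most tests will be falsely significant, or that stunted samples will look more diverse because they are older. That needs all visits pooled in one test, which the article does not state.
- That age at baseline is tied to socioeconomic status because "Newborn children will be identified using the Extended Program for Immunization (EPI) register". This is conjecture. The same section says that all families are registered with a health worker who visits them and that these workers help to approach participants.

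Finally, the 0–28 days is an eligibility window, not the distribution of age at stool collection. If most baseline stools came from a narrow age band, the baseline bias would be smaller. The article's disclaimer of causal claims does not answer the point, because an association produced by sampling age would still be misread as one with feeding or illness.

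**Conclusion.** The concern holds in limited form. The stated alpha-diversity test cannot adjust for age, no age term is given for the other methods, and the text does not say whether comparisons are within visit. Age at sampling can therefore confound associations with feeding, illness, antibiotic use, and unstandardised MUAC and head circumference, chiefly at baseline or if visits are combined.

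The true inflation cannot be determined from the article. Across assumed non-zero correlations of 0.2 to 0.6, the baseline false-positive rate runs from 5% to 75% per test at an unadjusted 0.05. A multiplicity-adjusted threshold would lower the rate for a single test but leave the bias in place. The rate is nominal when the exposure is unrelated to age, and near nominal at a later visit held to one age. The primary, descriptive objective is not affected, since age is its axis of interest.

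**What to change.** 1. Calculate age in days at each stool sample from date of birth and the sample date. Date of birth is recorded; confirm that the sample date is too, as the article does not say so.
2. For exposure associations with alpha diversity, replace the rank sum test with a regression model that includes age, allowing for a non-linear curve (log or spline). Add an infant random effect if visits are combined.
3. In ADONIS, enter age as the first term, with permutations that respect the infant when visits are combined. In metagenomeSeq, include age as a covariate.
4. State whether comparisons are made within visit, and report exposure associations by visit or conditional on age. Keep age in the baseline models even when the analysis is by visit.

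The cost is a change of analysis wording, with no new data beyond the sample date. The models lose a few degrees of freedom, and some associations seen without adjustment may shrink.

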### Dissemination

The results of the study will be disseminated to the public and academia, including our research team and collaborators, scientists, and the broader research community via participation in scientific conferences, meetings, and publications in peer-reviewed journals.

### Study status

The study began in 2024 and will continue until May 2026. As of October 2024, 70/70 (100%) were recruited. Data and samples were collected for the baseline (n=70) and first follow-up periods (3 months; n = 66).

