Our study has some limitations. First, the launch and implementation of a cohort study in remote, difficult-to-access rural areas are challenging, anywhere in the world, including Pakistan. As a result, dropout and attrition in the sample size are expected. Second, the study involved multiple assessments, requiring the mother to travel long distances in mountainous areas to reach the sampling site. The process is time-consuming and potentially burdensome to the mother and infants. However, these issues will be partly addressed by providing compensation for travel and sending advance reminders about follow-up visits using phone calls. Third, due to the self-reported and retrospective nature of the data collection during each visit, response and social desirability bias cannot be fully avoided. Finally, we could only identify the association between growth and gut microbiome development, but no causal relationship because of the non-interventional study design.

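### The rank sum test fixed for alpha diversity does not fit a within-infant objective in a cohort where losses are expected; comparisons across visits may partly reflect which infants attended

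*Protocol article*

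**What the plan says.** The Objectives section makes the primary aim longitudinal: to describe the development of the microbiota, and growth, in one group of infants from birth to two years. The Abstract gives the design: "A prospective cohort of mother-infant pairs (n=70) will be recruited from District Swat, Pakistan, and followed for two years". Data "will be collected at baseline and 3, 6, 12, 18, and 24 months", so each infant can contribute a baseline and five follow-up measurements.

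The article recognises that infants will be lost. Participants retention strategies warns of "systemic attrition, which can have a significant impact on the generalizability of the outcome of interest" and lists field measures against it: a residence criterion, local staff, reminder calls and tracing. The limitations in the Discussion add that "dropout and attrition in the sample size are expected".

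Study status gives the only counts. "As of October 2024, 70/70 (100%) were recruited", and "Data and samples were collected for the baseline (n=70) and first follow-up periods (3 months; n = 66"). It gives no reason for the difference of four.

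For alpha diversity, the Data analysis section fixes one method: "Differences in the alpha diversity will be estimated using the Wilcoxon rank sum test". It does not say which groups or visits are compared. ADONIS is named for composition and metagenomeSeq for abundance. No method is named for the growth trajectory.

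**The concern.** A question about development asks how the same infants change. The rank sum test compares two independent sets of values. Used between visits, it has three weaknesses here:

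- It discards the link between an infant's own samples, which carries most of the information about change.
- It treats two samples from one infant as if they came from two infants.
- It describes whoever attended each visit, and an infant seen at birth and at 3 months but not later contributes nothing to the later comparison.

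If the infants who stop attending differ in growth or microbiota from those who stay, a shift between visits mixes real change with a change in membership. The article itself argues that nutritional status and the microbiota influence each other, so both parts of the primary objective could shift together. The planned comparison with the Zimbabwean and Swiss cohorts would carry the same mixture.

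**Working it through.** **1. Inputs.** There are 70 infants at baseline and 66 at 3 months (Study status), with follow-up at 3, 6, 12, 18 and 24 months (Abstract). The article gives no sample-size calculation, dropout allowance or expected retention, so there is no figure of its own to reproduce.

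**2. Observed absence.** (70 − 66)/70 = 4/70 = 5.7%. The exact 95% interval is 1.6% to 14.0%.

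**3. Extrapolation (assumed).** With constant retention of 66/70 = 0.943, the proportion missing is 1 − (66/70)^k. Here k counts either follow-up visits or three-month periods.

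| Visit | k, same loss per visit | Missing | k, same loss per 3 months | Missing |
|---|---|---|---|---|
| 3 mo | 1 | 5.7% | 1 | 5.7% |
| 6 mo | 2 | 11.1% | 2 | 11.1% |
| 12 mo | 3 | 16.2% | 4 | 21.0% |
| 18 mo | 4 | 21.0% | 6 | 29.7% |
| 24 mo | 5 | 25.5% | 8 | 37.5% |

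At 24 months this leaves 70 × 0.745 ≈ 52 or 70 × 0.625 ≈ 44 infants.

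**4. How far that range can be trusted.** Missing at 24 months under other assumptions:

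| Assumption | Per visit | Per 3 months |
|---|---|---|
| Interval for 4/70 carried through | 7.6% to 52.9% | 12.0% to 70.0% |
| Loss rate halves after 3 months | 16% | 23% |
| Loss rate falls to a quarter after 3 months | 11% | 15% |
| Two of the four not yet due (66/68 retained) | 13.9% | 21.2% |
| The four are lost, nobody else is | 5.7% | 5.7% |
| All four not yet due | no observed loss | no observed loss |

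Some 24-month absence could also be administrative. "The study began in 2024 and will continue until May 2026", so an infant enrolled after May 2024 would not complete 24 months by then. Enrolment dates are not given.

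**5. What the rank sum test does with such data.** Comparing baseline with 3 months, it takes 70 + 66 = 136 values as independent, although they come from 70 infants. If the absent infants are simply those seen earlier and then lost, 66 infants appear twice and 4 once. With 52 left at 24 months, it takes 70 + 52 = 122 values, and 18 infants stand on the baseline side only. With 44 left, it takes 70 + 44 = 114 values, and 26 infants stand on the baseline side only. A shift between the two sides then includes any difference between those 18 or 26 infants and the rest.

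A mixed model fitted to all visits keeps the pairing. It also uses the earlier measurements of infants later lost when it estimates the later means. Its estimates are valid if loss can be explained by the data already observed. The pairing problem in this step exists at any level of loss; the membership problem grows with loss.

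**The case against.** **Silence is not a finding.** This is a journal article, and a fuller protocol or analysis plan may hold the missing-data rules, reason codes for missed visits and a comparison of retained with lost infants. That stands: their absence here is not counted as an error. The article also never says that lost infants will be excluded. However, the Data analysis section is not silent on method. It commits to a named test, and that choice can be judged.

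**The rank sum test may be meant for groups at one visit.** The article does not say what is compared. For delivery mode at a single visit, for example, the samples are independent and the pairing objection falls away. No other alpha-diversity test is named for the primary, longitudinal question, so the mismatch with that objective remains.

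**Stronger readings the documents do not support.**

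- A reader might infer that the article's figures forecast 25% to 38% loss. They do not: the range comes from one interval and four unexplained absences, extended at an assumed constant rate. A missed visit may also be followed by a return, since tracing and home visits are planned.
- A reader might infer that the trajectories will be biased towards healthier infants. That requires loss to depend on growth or microbiota, and no data are given on this. The reasons offered are relocation, loss of interest, distance and terrain.
- A reader might put a size on the bias in mean height-for-age or in stunting. The article fixes no estimator for either. It also gives no standard deviation, correlation between visits or relation of loss to size, so any such figure would rest on invented inputs.
- A reader might say the article sees attrition only as lost numbers. The limitations read that way, but the retention section names the threat to generalizability.

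**Conclusion.** The concern holds in a limited form. For a primary objective about change within infants, the one alpha-diversity test fixed ignores the pairing of repeated samples and uses only infants present, while the article itself expects attrition. Comparisons across visits may therefore partly reflect changing membership.

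The observed size is 4 of 70 (5.7%) without 3-month data, cause unknown. By 24 months the absence would be about 25% or 38% if that rate held per visit or per three months. It could be as low as about 6%, and there is no observed loss if all four were not yet due. The direction and size of any resulting bias cannot be taken from the documents. The case for changing the method does not depend on the extrapolation, because a model that uses within-infant information is better suited to the objective even with little loss. The change is worth making, with medium confidence.

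**What to change.** In the Data analysis section, name a likelihood-based longitudinal mixed model as the method for the alpha-diversity and growth z-score trajectories. It should have:

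- a random effect for infant and a visit effect;
- all 70 infants and every available visit, including the earlier visits of infants later lost;
- baseline length and weight z-scores and location in the model. In the growth model the baseline z-score enters as the first repeated measurement; in the alpha-diversity model it is a covariate, with visit means averaged over all 70 infants.

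The rank sum test can stay for comparing independent groups at a single visit, if the text says so.

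Label raw summaries by visit, including the composition results, as describing the infants attending that visit. Alongside them, report deaths separately from other loss, and show the baseline characteristics of retained and lost infants. Inverse-probability weighting is not needed; with as few as four losses, a model for attendance could be unstable.

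The cost is a few sentences and modest extra programming, with no new participants, samples or visits. The limitation to state is that the model relies on loss being explained by the observed data, which cannot be verified from those data.
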